N = 65 Richartz et al. 1998 [8]	Prospective; Rejection during in-hospital period	1. Mean QT_C _= 449 ± 2 ms without rejection; 517 ± 11 ms with rejection (*p *< 0.001) 2. > 10% increase in QT_C _predicted rejection with sensitivity, 86%; specificity, 88%	1. Only observed rejection during hospitalization for transplant surgery 2. Analyzed only 3 ECGs per subject 3. ECG analyzers not blinded from clinical information about rejection	An increase in the QT interval predicts acute allograft rejection

N = 52 Kolasa et al. 2005 [9]	Retrospective; Long-term mortality over 7 yrs	Poorer survival over 7 yrs in subjects who had a > 10 ms per year change in their QT_C _interval on their annual ECG	1. Link to rejection not studied 2. Analyzed only one ECG per year	As little as a 10 ms change in the QT interval is linked to mortality

N = 200 Tenderich et al. 2006 [10]	Retrospective; Rejection during first 3 months	> 25 ms increase in QT_C _interval predicted acute allograft rejection with sensitivity, 77%; specificity, 96%.	1. Only analyzed 2 ECGs per subject 2. ECG analyzers not blinded from clinical information about rejection	Increase in QT interval predicts acute rejection during the period of interest

N = 587 Vrtovec et al. 2006 [11]	Retrospective; Long-term mortality up to 17 yrs	1. Patients with ≥ 10% increase in QT_C _interval between 1^st ^and 2^nd ^year post-transplant had 6.86 times higher risk of dying.2. ≥ 10% increase in QT_C _was the only independent predictor of long- term mortality on multivariate analysis 3. Trend was a decreasing QT_C _over the yrs suggesting sympathetic reinnervation	1. Link to rejection not studied 2. Analyzed only one ECG per year	An increase in the QT interval is linked to mortality

N = 71 Vrtovec et al. 2008 [12]	Retrospective; 1- year all-cause & SCD mortality in subjects with severe acute rejection	1. QT_C _was longer in SCD group than in survivors (475 ± 57 versus 437 ± 36 ms; *p *= 0.02) 2. Patients who had > 10% increase in QT interval during a severe acute rejection episode were at increased risk for SCD.	1. Limited to just patients with severe rejection; unable to tell whether increased QT interval could predict earlier, milder forms of rejection 2. Analyzed just 2 ECGs per subject (one at baseline 7 days after surgery, second at time of rejection)	An increase in the QT interval is linked to mortality

ms = millisecond; SCD = sudden cardiac death; QTc = QT interval corrected for heart rate

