## Methods/design

### Design

The NEW HEART study is a prospective, double-blind, multi-center descriptive research study. The primary aims of the NEW HEART study are to: 1) determine whether an increase in the QT interval during the first 6 months following heart transplant is a sensitive and specific biomarker for acute allograft rejection; 2) determine the timing of initial increased QT interval relative to biopsy-diagnosed stages of mild, moderate, and severe allograft rejection.

Secondary aims are to: 1) determine whether an increase in the QT interval during the first 6 months following heart transplant predicts mortality within the first year, and 2) explore additional ECG measurements that might predict acute allograft rejection or death.

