### Analysis of ECG monitoring data

The ECG will be sent to a large server hosted by the UCSF Office of Academic and Administrative Information Systems (OAAIS). The server is a secure, highly redundant data center with 24/7 availability due to back-up generators that protect against power outages. The system provides nightly data backup. Investigators in the [name] Lab will access the ECG data by logging on with a username and password via a Virtual Private Network (VPN), which encapsulates data transfers between networked devices not on the same private network and keeps the transferred data private from other devices. Investigators who analyze the daily ECG data will be blinded from all information regarding the subject's clinical status and biopsy results. In addition, pathologists who grade the biopsies and clinicians who provide medical care in the transplant clinics will be blinded from the QT interval monitoring data.

QT and RR intervals will be made in a computer-assisted manner. The Aerotel measurement software provides a zooming feature to enlarge ECG waveforms for better visualization. In addition, electronic calipers are provided so that the researcher will select the appropriate waveform onset and offset points and the computer software will provide the interval value in milliseconds (ms). The QT interval will be measured from the onset of the QRS waveform to the end of the T waveThe end of the T wave will be defined as the intersection of a tangent to the steepest slope of the last limb of the T wave and the baseline (Figure 2) [18]. A standardized correction to account for the effect of HR will be applied (QT_C_). An increase in the QT_C _interval from the previous day of at least 25 ms that persists for 3 consecutive days will be considered abnormal [10].

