### Statistical analysis

Using the variable definitions in Table 2, a logistic regression analysis will be performed with the independent variable being presence/absence of the ECG criteria (ΔQT_C _≥ +25 ms × 3 days [10]) and the dependent variable being presence/absence of acute allograft rejection. Odds ratios and confidence intervals will be reported as well as the universal proportions used to determine the value of new diagnostic criteria (sensitivity, specificity, positive/negative predictive value, and predictive accuracy, Table 3).

**Table 2 T2:** Variable definitions for statistical analysis

Variable	Definition	Type of Variable
ΔQT_C_	≥ +25 ms increase in QT_C _interval from previous day lasting 3 consecutive days [10]	Continuous (expected range, 10-100 ms)

Acute allograft rejection	EMB category 1R or 2R or 3R with confirmation by treating physician	Categorical; dichotomous (yes/no) No = 0; Yes = 1R or 2R or 3R

Days to rejection	Number of days from first positive ECG criterion to mild, moderate, or severe rejection diagnosis. If the ECG criterion follows rejection, a negative # of days will be reported.	Continuous (expected range -365 to +365)

Acute rejection severity	EMB category: 1R (mild), 2R (moderate), 3R (severe)	Categorical

Cardiac rhythm	Sinus rhythm, atrial fibrillation, atrial flutter, junctional rhythm	Categorical

Heart rate	Heart rate per minute calculated from 30 s rhythm strip	Continuous (expected range, 60-120)

P wave duration	Interval from beginning to end of P wave in ms (measure of intra-atrial conduction delay)	Continuous (expected range, 70-126 ms)

QRS duration	Interval from beginning to end of the QRS waveform	Continuous (expected range, 72-160 ms)

PR interval	Interval from the beginning of the P wave to the beginning of the QRS complex measured in ms. PR interval > 200 ms indicates an abnormal delay of conduction (1^st ^degree AV block).	Continuous (expected range, 112-240 ms)

QRS amplitude	Height of QRS waveform in μV	Continuous (expected range, 500-1000 μV

T_PEAK _- T_END_	Interval from the peak of the T wave (or nadir in inverted T waves) to the end of the T wave in ms. Prolonged T_PEAK _-T_END _indicates heterogeneity of repolarization and risk for arrhythmia	Continuous (expected range, 112-240 ms)

**Table 3 T3:** Definitions of Universal Proportions

Criterion	Definition
Sensitivity	Proportion of those with acute rejection who are positive for the ECG criterion

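### Primary aim 1 asks about a QT increase in general but scores rejection on one previous-day 25 ms rule, so the pre-specified analyses could not separate a failed rule from a failed marker

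*Protocol article*

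**What the plan says.** The Design section of the protocol article words primary aim 1 without a threshold: to "determine whether an increase in the QT interval during the first 6 months following heart transplant is a sensitive and specific biomarker" for rejection.

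The section on analysis of ECG monitoring data then fixes one rule. A rise in the QTc "interval from the previous day of at least 25 ms that persists for 3 consecutive days will be considered abnormal". Under Statistical analysis, "a logistic regression analysis will be performed with the independent variable being presence/absence of the ECG criteria", that is, yes or no on this rule. The same rule feeds sensitivity, specificity, predictive values and predictive accuracy in Table 3, and the description of timing relative to biopsy. The exploratory ECG variables include no other definition of a QTc rise.

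Table 1 in the Background lists two studies that report accuracy for rejection:

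- The prospective one (N = 65) used a rise of more than 10%: "rejection with sensitivity, 86%; specificity, 88" per cent. Its listed limits are in-hospital rejection only, 3 ECGs per subject and unblinded reading.
- The source cited for the 25 ms rule (N = 200) is described as "Retrospective; Rejection during first 3 months". Its rule "predicted acute allograft rejection with sensitivity, 77%; specificity, 96" per cent. Its listed limits are 2 ECGs per subject and unblinded reading.

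**The concern.** The question is general, but the planned answer rests on one cut-off, one reference point (yesterday) and one persistence requirement. The cited source had only 2 ECGs per subject, so its reported accuracy cannot speak to a day-on-day step held for 3 days in a daily series.

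If that rule performs poorly, there are at least two explanations. QTc may carry little information about rejection, or it may carry information in a form that the rule does not capture, such as a rise that builds over several days. The pre-specified analyses contain nothing that would distinguish them. The Discussion presents the study as a step towards fewer biopsies and possibly a randomized trial, so a poor result blamed on the marker when the rule was at fault could end work on a usable signal.

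**Working it through.** The plan states no figure of its own to reproduce on this point; the published accuracies are taken as printed in Table 1.

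**1. The two cut-offs on one scale.** Table 1 gives a mean QTc of 449 ms without rejection.

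- 0.10 × 449 = 44.9 ms
- 25 / 449 = 5.6%
- The cut-offs coincide only at 25 / 0.10 = 250 ms.

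At any realistic QTc the 10% cut-off is therefore the stricter one.

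**2. Published accuracy (Youden index = sensitivity + specificity − 1).**

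- 25 ms rule: 0.77 + 0.96 − 1 = 0.73
- More than 10%: 0.86 + 0.88 − 1 = 0.74

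The document's own evidence does not favour scoring only one of them.

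**3. A gradual rise.** Table 1's gap is 517 − 449 = 68 ms, and 68 / 449 = 15%. Treating this difference in means as the size of one patient's rise is an assumption. Daily step if the rise is even:

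| Days to reach 68 ms | Step per day | At least 25 ms? |
|---|---|---|
| 1 | 68.0 | yes |
| 2 | 34.0 | yes |
| 3 | 22.7 | no |
| 5 | 13.6 | no |
| 7 | 9.7 | no |

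Without noise, a rise spread evenly over 3 or more days never meets the 25 ms previous-day step, although it ends 15% above baseline.

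**4. The same with noise.** Simulation of 20,000 patients with independent normal day-to-day variation. The document gives no within-patient SD, so it is an assumption shown over a range. Persistence is read as all 3 days lying at least the threshold above the day before the rise. The baseline is the mean of the first 7 recordings, also an assumption.

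True rise of 68 ms over 7 days, then a plateau:

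| SD (ms) | 25 ms from previous day | More than 10% over baseline |
|---|---|---|
| 6 | about 14% detected | over 99% |
| 8 | about one third | over 99% |
| 10 | about one half | over 99% |

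Detection by the 25 ms rule improves with noise only because chance dips create larger steps.

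No rejection, 180 daily readings, share of patients ever flagged:

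| SD (ms) | 25 ms from previous day | More than 10% over baseline |
|---|---|---|
| 5 | 0.03% | under 0.1% |
| 6 | 0.3% | under 0.1% |
| 8 | 10% | under 0.1% |
| 10 | 43% | under 0.1% |
| 12 | 79% | under 0.1% |
| 15 | 98% | under 0.1% |

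The baseline column assumes no slow drift in QTc, so it is a best case.

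**5. Precision of the added test.** With 325 patients and the 25–35% rejection rate given under Diagnosis of acute allograft rejection, 325 × 0.25 = 81 and 325 × 0.35 = 114 patients reject. A sensitivity of 86% would have a Wilson 95% interval of about 77–92% (n = 81) to 79–91% (n = 114). A specificity of 88% would have about 83–92%. No extra patients are needed.

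**The case against.** Fixing one cited threshold in advance is sound practice and prevents a cut-off being picked from the data. The choice of source is also defensible: its study is larger (200 against 65) and covers the period of interest, whereas the prospective study saw only in-hospital rejection. Neither was read blind. All of this stands, and it is why the 25 ms rule should remain primary. Further cut-offs or an ROC analysis might sit in an analysis plan that is not shown. That limits the weight of the point, but the article itself names the predictor and the cut-off, and they are narrower than the aim.

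Three stronger readings are tempting and are not supported.

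- **That the 25 ms cut-off is the less sensitive one.** A reader might infer this from 77% against 86% and project missed rejections onto the 325 patients. Those figures come from two different cohorts. On the same ECGs, with the same reference and persistence, every rise of more than 10% is also a rise of at least 25 ms (step 1). In the simulation no patient was flagged by a 45 ms previous-day rule alone. On that reference the 10% rule cannot find more rejections; any gain in sensitivity comes from changing the reference to a baseline.
- **That daily use will swamp the rule with false positives.** This needs an assumed SD of about 10 ms or more. At 6 ms or below, fewer than 1% of patients are flagged. The article argues that variation is small in denervated hearts, although it gives no figure.
- **That the study could never tell the two explanations apart.** Daily QTc is measured in milliseconds, and Table 2 even types the change as continuous, so other rules can be scored afterwards. They would not be pre-specified, and accuracy at a cut-off chosen after seeing the results is optimistic.

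**Conclusion.** The point holds in a limited form. Aim 1 is wider than its analysis: every planned QTc analysis of rejection rests on one dichotomy, and the rise of more than 10% from Table 1's only prospective study is not scored despite near-equal published performance (0.74 against 0.73). If the single rule does poorly, the pre-specified analyses cannot say whether the rule or the marker failed.

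The firmest ground is the reference point. A 68 ms rise spread evenly over 3 or more days stays below the daily step by arithmetic alone. With a 7-day rise and SD 6 ms, about 14% of such patients meet the rule, against over 99% for a baseline comparison. This rests on rises being gradual, on the Table 1 gap representing an individual's change, and on independent noise without drift; the documents establish none of these. The false-flag side depends on the SD and should be presented as conditional.

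The change is worth making before the data are analysed. It does not invalidate the primary analysis.

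**What to change.** Keep the 25 ms rule as primary. Under Statistical analysis, add to aim 1 a named secondary index test: a QTc rise of more than 10% over a fixed patient baseline, held for 3 consecutive days and scored from the same blinded readings. Define the baseline explicitly, for example as the mean of the first week of recordings. It must not be the previous day, because on that reference the 10% rule is nested within the 25 ms rule.

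Report all Table 3 proportions for both rules, with a paired McNemar comparison done separately in rejecting and non-rejecting patients. State that the rules differ in both reference and cut-off, so a difference between them cannot be credited to the cut-off alone.

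The cost is analysis wording and one additional test, labelled secondary. It needs no new patients, recordings or unblinding.

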Specificity	Proportion of those without rejection who are negative for the ECG criterion

Positive Predictive Value	Proportion of patients with positive ECG criterion who have rejection

Negative Predictive Value	Proportion of patients with negative ECG criterion who do not have rejection

Predictive Accuracy	$\frac{\#\text{true positives}\pm \text{true negatives by the ECG criterion}}{\text{Total }\#\text{ of patients enrolled in the study }\times \text{ 1}00}$

Descriptive statistics (means ± SD) will be used to describe the average time period between the development of the ECG criterion and biopsy evidence of rejection. In addition, we will report the proportion of subjects who develop the ECG criterion (≥ +25 ms increase in QT interval from previous day lasting 3 consecutive days [10]) before, during, or after the stages of mild, moderate, and severe rejection.

The Kaplan-Meier method with the log-rank test will be used to estimate survival curves over one year and to compare all-cause mortality in patients who are positive or negative for the QT_C _criterion. Cox Proportional Hazard modeling will be used to control for baseline differences between groups and for tacrolimus use.

Logistic regression will be used with the dependent variables of rejection (yes/no) and all- cause mortality (yes/no). In both regressions, tacrolimus dosage (with "0" entered if the patient is not receiving tacrolimus) will be included as a covariate in the model. If any of the explorative variables are statistically significant, a multiple logistic regression model will be used including the ECG criterion of interest to determine whether additional ECG criteria are independent predictors of rejection and death.

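### The ΔQTc row of Table 2 merges a yes/no criterion with a continuous measurement, and the described analyses test only one borrowed cut-off

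*Protocol article*

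**What the plan says.** All places are in the Protocol article.

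- **Statistical analysis, Table 2, ΔQTc row.** The definition is a rise of at least 25 ms in the QTc "interval from previous day lasting 3 consecutive days [10". The type in the same row is "Continuous (expected range, 10-100 ms".
- **Statistical analysis, first paragraph.** "Using the variable definitions in Table 2, a logistic regression analysis will be performed", with "the independent variable being presence/absence of the ECG criteria".
- **Statistical analysis, Table 3.** Sensitivity is "Proportion of those with acute rejection who are positive for the ECG criterion". Specificity, the predictive values and accuracy rest on the same positive/negative status.
- **Statistical analysis, after Table 3.** The timing summaries count from, or classify by, the criterion being met. The Kaplan-Meier analysis is to "compare all-cause mortality in patients who are positive or negative for the" QTc criterion.
- **Design, primary aim 1.** The question is whether an increase in the QT interval "is a sensitive and specific biomarker for acute allograft rejection". The aim names no threshold.
- **Background, Table 1.** In the study from which the cut-off comes, a rise of more than 25 ms in the QTc "interval predicted acute allograft rejection with sensitivity, 77%; specificity, 96" percent. Its listed limitations include only two ECGs per subject. Another rejection study in that table used a rise of more than 10%.

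**The concern.** Table 2 is named as the source of the variable definitions for the regression, so its type column matters. An analyst who follows the type would fit an odds ratio per ms. One who follows the text would fit an odds ratio for criterion met versus not met. These are different quantities for the primary predictor.

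The second issue follows from the first. The ms value is listed as continuous, but no described analysis uses it. Aim 1 is about QT increase as a biomarker, whereas the described analyses examine one rule. That rule carries a threshold from a two-ECG retrospective study into daily home recordings, with a previous-day reference and a three-day persistence requirement. If it performs poorly, the described results would not show whether the threshold was badly placed or QTc change carries little signal.

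**Working it through.** **1. The contradiction (no model needed).** The definition requires at least 25 ms. The stated range is 10 to 100 ms, which is 90 ms wide. Values from 10 up to 25 ms cannot meet the definition: 25 − 10 = 15 ms, and 15/90 = 17% of the range. A variable that records whether a threshold was met also has no ms range at all.

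**2. How unsettled the cut-off is in Table 1.** The other rejection study used more than 10%. At its quoted mean of 449 ms without rejection, 0.10 × 449 = 44.9, or about 45 ms, against 25 ms here.

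**3. Share of patients positive, from the article's own figures.** The inputs are sensitivity 0.77 and specificity 0.96 (Table 1), and rejection in the first 6 months of 25% to 35% (Diagnosis of acute allograft rejection). The formula is p = prevalence × 0.77 + (1 − prevalence) × 0.04.

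- At 25%: 0.1925 + 0.0300 = 0.2225
- At 35%: 0.2695 + 0.0260 = 0.2955

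**4. Information kept by the split.** The article gives no figure for this, so there is none to reproduce. For a normal predictor with a weak linear effect, the efficiency of a split with share p positive, relative to the continuous value, is φ(z)² / [p(1 − p)]. Here z is the normal quantile at 1 − p and φ is the normal density.

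- p = 0.2225: z = 0.764, φ = 0.2980; 0.0888 / 0.1730 = 0.513, so 48.7% is lost
- p = 0.2955: z = 0.537, φ = 0.3453; 0.1192 / 0.2082 = 0.573, so 42.7% is lost

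As an equivalent number of the 325 patients: 0.513 × 325 ≈ 167 and 0.573 × 325 ≈ 186.

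**5. Sensitivity to the positive share.** The share under the daily three-day rule is unknown, so a range is shown.

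| Share positive (assumed) | Efficiency | Lost |
|---|---|---|
| 5% | 0.224 | 78% |
| 10% | 0.342 | 66% |
| 20% | 0.490 | 51% |
| 30% | 0.576 | 42% |
| 50% | 0.637 | 36% |

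Efficiency equals 0.50 at p ≈ 0.209. The loss exceeds half only if fewer than about 21% of patients are positive.

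**The case against.** The best defence is that the row is a labelling slip. The criterion is worded consistently in the Abstract, in the section on analysis of ECG monitoring data and in the Statistical analysis section. The text says plainly that presence or absence enters the model, so few readers would mistake the primary analysis. This largely stands: the intended primary analysis can be recovered. The row is still wrong on its face, and it belongs to the table that the regression is told to use.

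A reader might infer that a binary predictor is itself the error. The article does not support that. Sensitivity, specificity and predictive values need a positive/negative test, and fixing the cut-off in advance avoids the optimism of choosing it from the same data. Table 1 also gives a reason for the 25 ms choice: its source covered the post-transplant period of interest, while the 10% study covered only the in-hospital stay.

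A reader might also infer that other cut-offs are foreclosed. They are not. Intervals are measured in ms every day and the ECGs are kept. A fuller analysis plan, not shown, may already contain a continuous or ROC analysis, so its absence from a condensed article is not a fault in itself.

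Finally, the efficiency formula fits this setting poorly. The cited 77% and 96% imply an odds ratio of (0.77 × 0.96) / (0.23 × 0.04) ≈ 80, which is not a weak effect, and a sustained ΔQTc need not be normal. The percentages are therefore indicative only.

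**Conclusion.** The point holds as a definition error with a modest analytic consequence. One row of Table 2 combines a dichotomous definition, a continuous type and a range that begins 15 ms below the defining threshold. The model and all other described uses of the predictor are binary. Read as written, the analyses can judge this one rule but cannot separate a poor cut-off from an uninformative marker.

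It is tempting to conclude that the plan discards most of the information in its primary predictor. That is not established. With the article's own sensitivity, specificity and rejection rates the loss is about 43% to 49%, a little under half. It passes half only if fewer than about 21% of patients meet the criterion, which is possible under a stricter daily rule but is an assumption. All these figures rest on a normal predictor with a weak linear effect, and on the cited performance carrying over to daily home recordings.

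**What to change.** Split the ΔQTc row of Table 2 into two variables and state which one enters each model:

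- **(a) ECG criterion met**, dichotomous. Keep it as the pre-set primary rule for sensitivity, specificity, predictive values and the main logistic model.
- **(b) Sustained ΔQTc in ms**, continuous, with an expected range not tied to the 25 ms cut-off.

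Add, as secondary, a logistic model with (b) as a continuous term, and an ROC curve with AUC and confidence interval. Do not define (b) simply as the largest value over all recordings. A maximum tends to rise with the number of recordings, so it would partly reflect adherence and length of follow-up. Take it over a fixed window, for example before each biopsy, or account for the number of recordings.

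The cost is a corrected table row and a little more analysis on data already measured. No new data and no change to the primary rule are needed.

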### Procedures

Participants will be recruited either while they are in the hospital for transplant surgery, or if that is inconvenient, during their first clinic visit following transplant surgery. After informed consent is obtained, demographic and clinical data will be collected by self-report and by medical record audit. At the time of each EMB, data from the medical record will be abstracted to confirm current medications, serum levels of anti-rejection medications, clinical data regarding EMB results, and other clinical data reflecting myocardial performance consistent with rejection status. Only one anti-rejection medication (tacrolimus) is associated with an increased QT interval. If a patient is on chronic tacrolimus therapy without a change in dosage, it should not interfere with the daily ECG monitoring measurement because we will be comparing each patient with him/herself and noting any change from the previous day's QT interval. However, we will track initiation or change in any QT-prolonging drug. On their website, the Arizona Center for Education and Research on Therapeutics [15] maintains a comprehensive list of QT- prolonging drugs that we have incorporated into the medications section of our electronic database system. Further, on a quarterly basis, we will continue to reference this website for new drugs as they come to market and update our data capture to include those associated with QT-prolongation.

The other drug class that patients may be taking is 3-Hydroxy-3-Methyl-Glutaryl Coenzyme A Reductase inhibitors (i.e., statins) which are known to shorten the QT interval. Thus, we will also monitor statin therapy. To insure patient safety, we will notify patients' transplant cardiologists within 48 h of the detection of any QTc interval exceeding the population 99th percentile for adult males (> 470 ms) or females (> 480 ms) [16].

At the time of informed consent and enrollment, subjects will receive the HeartView™ recorder and its companion Internet Transmitter, which will transmit the subject's ECG as described earlier. Subjects will be asked to record a 10-s 8-lead ECG daily for 6 months.

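### Days to rejection pairs a patient's first ECG alarm with a rejection diagnosis up to a year away in either direction, so the planned timing summaries for primary aim 2 cannot separate early warning from coincidence

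*Protocol article*

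**What the plan says.** Primary aim 2 (Design) is to "determine the timing of initial increased QT interval relative to biopsy-diagnosed stages of mild, moderate, and severe allograft rejection".

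The variable that serves it is days to rejection in Table 2:

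- It is the "Number of days from first positive ECG criterion to mild, moderate, or severe rejection diagnosis".
- On order, "If the ECG criterion follows rejection, a negative # of days will be reported".
- Its type and range, in days, are "Continuous (expected range -365 to +365".

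The Statistical analysis section plans two summaries. The first is a mean: "Descriptive statistics (means ± SD) will be used to describe the average time period between the development of the ECG criterion" and biopsy evidence of rejection. The second is the proportion of subjects who meet the criterion "before, during, or after the stages of mild, moderate, and severe rejection".

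The two observation periods differ. On ECGs, Procedures says "Subjects will be asked to record a 10-s 8-lead ECG daily for 6 months", starting at enrolment, which is within six weeks of transplant. Rejection episodes, by number and grade, are collected for one year after surgery (Follow-up and end-points).

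**The concern.** The clock starts at a patient's first positive criterion, whether or not that alarm has anything to do with the rejection it is paired with. A chance alarm in week 2 and an unrelated rejection in month 8 would count as a lead of more than 200 days. The article does not say which episode is used when a patient has several, whether an alarm that came to nothing can be set aside, or what values chance alone would produce.

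Two features move the result away from zero when alarm and rejection are unrelated. ECG recording ends about half a year before rejection follow-up does, which favours positive values. Taking the earliest alarm favours them further, and more so the more often alarms occur. Early rejection works in the opposite direction. Averaging signed values also lets true leads and lags offset each other within the mean.

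Early detection is the novelty that the article claims over previous studies (Background and Discussion), and aim 2 is where it is examined. A positive mean, or a majority of alarms classed as before, would naturally be read as early warning although either could arise by chance.

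**Working it through.** The article gives no expected lead time or precision for this variable, so there is no figure to reproduce. The check asks what the two summaries show when alarms and rejection are independent.

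**Inputs from the article:** ECG recording for 6 months (taken as 182 days) from enrolment; enrolment within 6 weeks (42 days) of transplant; rejection collected to day 365; biopsies weekly or biweekly for two to three months, then less often; N = 325; 26% with rejection in the first year.

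**Assumptions, not in the article:** the number or rate of chance alarms and the distribution of rejection times.

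**1. Simplest case.** One alarm uniform on 0-182 days, rejection uniform on 0-365 days, both counted from the same day.

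- Mean = 365/2 - 182/2 = 182.5 - 91 = +91.5 days
- SD = √[(182² + 365²)/12] = √(166,349/12) = 118 days
- Proportion before = 1 - 91/365 = 75%

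**2. Rejection concentrated early.** Rejection exponential with parameter m, truncated at 365 days, has mean m - 365e/(1 - e), where e = exp(-365/m). The first of k uniform alarms has mean 182/(k + 1): 91, 60.7 and 45.5 days for k = 1, 2, 3. The mean interval is the difference. The percentage of alarms before rejection, in brackets, is from simulation.

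| m (days) | Mean rejection day | k = 1 | k = 2 | k = 3 |
|---|---|---|---|---|
| 120 | 101.7 | +10.7 (49%) | +41.0 (62%) | +56.2 (70%) |
| 90 | 83.6 | -7.4 (42%) | +22.9 (56%) | +38.1 (64%) |
| 60 | 59.2 | -31.8 (31%) | -1.5 (45%) | +13.7 (54%) |

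**3. Staggered enrolment and a biopsy schedule.** Simulation of 400,000 patients per scenario: enrolment uniform on days 7-42; constant alarm hazard giving 10% to 95% of patients a first alarm within 182 days; rejection after enrolment; diagnosis at the next biopsy (weekly to day 91, then about every 30 days).

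| Rejection timing | Mean (days) | SD (days) | Before |
|---|---|---|---|
| Uniform, enrolment to day 365 | +94 to +132 | 110-114 | 77-87% |
| Equal chance at each biopsy | +32 to +70 | 114-118 | 53-69% |
| Uniform, enrolment to day 182 | about 0 to +38 | 66-73 | 50-72% |

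Within each row, the mean rises with the alarm rate.

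**4. Effect of a window.** In the step 3 scenarios, counting an alarm only if it falls in the 14 days before diagnosis (an illustrative length) leaves 4-8% of unrelated pairs as leads, against 50-87% without a window.

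**5. Numbers contributing.** 325 × 0.26 = 84.5 patients with rejection. If 30% to 80% of them have any alarm (assumed), about 25 to 68 patients supply an interval.

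**The case against.** Several points on the other side are sound.

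- **The mean is not the only analysis.** A reader might infer that the signed mean is all that aim 2 has. It is not: the proportions before, during or after each grade are also planned, and they show leads and lags separately. They answer the cancellation point, but they too state no window, so the chance problem remains.
- **The pull is not always positive.** A reader might infer that the variable must show a lead. Step 2 includes negative values. The +91.5 days rests on rejection spread evenly over the year, which the article does not support: it cites 26% rejection in the first year (Background) and 25 to 35% in the first six months (Diagnosis of acute allograft rejection), leaving few first rejections for later. Steps 1 and 2 also start both clocks on the same day. If rejection is counted from transplant and ECGs start up to 42 days later, those means fall by up to 42 days.
- **The biopsy date is a legitimate endpoint.** One might object that rejection begins at an unknown time between biopsies. But aim 2 and Table 2 concern biopsy diagnosis, whose date is known. Time from true onset is a different question.
- **Association is tested elsewhere and aim 2 is descriptive.** The logistic regression and the sensitivity and specificity do address association, but per patient, so they say nothing about timing.
- **An article condenses.** A pairing rule might sit in an analysis plan not shown. However, the article does fix the start of the interval, a full-year range either way and the summary statistic. Followed as written, these mislead.

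**Conclusion.** The point holds in this form: neither the signed mean nor the before/during/after proportions can separate early warning from coincidence for primary aim 2, because no pairing window and no chance reference are stated.

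Under independence the mean lay between about -32 and +132 days, and the proportion before between 31% and 87%. These are results of assumed scenarios, not bounds; the alarm frequency and rejection timing that determine them are not in the article. With rejection confined to the first six months, which is nearer to the rates cited, the null mean was about 0 to +38 days. The supportable conclusion is that the null value is unknown and may be far from zero in either direction, not that the study will show a false lead of a particular size.

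**What to change.** Change the definition of days to rejection and its analysis before the ECG and biopsy data are linked:

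1. Define lead time per rejection episode, from a criterion onset inside a pre-stated look-back before the diagnosing biopsy, for example since the last biopsy without rejection. Add longer windows as sensitivity analyses. Class episodes with no onset in the window as not preceded.
2. Report, by grade, the proportion of episodes preceded and the median and IQR of the lead to biopsy diagnosis, in place of one signed mean ± SD.
3. Give a chance reference: the alarm rate in windows of equal length ending at negative biopsies, or the same statistics with alarm dates permuted within patient.

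The cost is revised wording and modest programming; daily ECGs and biopsy results are already collected. There are two drawbacks. Some episodes will have no lead time. The window also caps the longest lead that can be measured: with weekly or biweekly biopsies, a look-back to the previous biopsy allows only 7 to 14 days, and a true longer lead would be scored as not preceded. The longer sensitivity windows are there for that reason.
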